### Interventions

2.4

The participants will be randomly divided into 2 groups: the experimental group and the control group. The experimental group will receive thread embedding treatment 6 times (1 time/week) in 6 weeks on 14 defined knee areas, and the control group will receive acupuncture treatments 12 times (2 times/week) in 6 weeks on 9 defined acupuncture points.

#### Experimental group

2.4.1

The TEA (29 gauge∗40 mm, 27 gauge∗60 mm, polydioxanone suture) was manufactured by Mircacu, feeltech Inc. Gunsan, Republic of Korea (Fig. 2). After disinfecting one side of the more painful area, KMD will perform the above embedding thread on the treatment region (Fig. 3). A total of 14 embedding threads will be used per participant. Therefore, the points of the TEA in this study will be as follows.

(1)6 cm(a)Vastus lateralis. 1 horizontal needling upwards from ST34(b)Muscle vastus medialis. 1 horizontal needling upwards from SP10(c)Medial collateral ligament. 1 horizontal needling towards the direction of medial epicondyle of femur(d)Pes anserinus. 1 horizontal needling from Spleen 9 along the pes anserinus(2)4 cm(a)Side of patella. 4 horizontal needlings along the upper outer, upper inner, lower outer, and lower inner of patella(b)Lateral collateral ligament. 1 horizontal needling in the direction of lateral epicondyle of femur along the lateral collateral ligament(c)Lateral joint line. 1 horizontal needling toward the lateral back along the lateral joint line(d)Medial joint line. 2 horizontal needlings toward the medial back along the medial joint line(e)Medial collateral ligament. 1 horizontal needling toward the direction of medial epicondyle of femur(f)Pes anserinus. 1 horizontal needling from Spleen 9 along the pes anserinus

**Figure 2 F2:**
[figure not shown]
TEA used in clinical trial.

**Figure 3 F3:**
[figure not shown]
The point of TEA.

#### Control group

2.4.2

The participants of control group will receive acupuncture intervention with 0.30 × 40 mm disposable sterilized stainless steel acupuncture needles (DongBang Acupuncture Inc., Republic of Korea), done by KMD. On one side of the more painful area, the acupuncture needles will be inserted perpendicular to a depth of 5 to 20 mm into the muscles for 20 ± 5 minutes.

In this study, the 9 acupuncture points will be used: unilateral ST34, SP09, SP10, Ex-LE04, Ex-LE02, LR08, ST36, GB33, and Ex-LE05, which will be affected as a result of acupuncture treatment on patients with knee osteoarthritis in clinical treatment.

### Outcome measurement

2.5

A series of measurements to assess VAS for pain and short form McGill pain question (SF-MPQ), Western Ontario and McMaster Universities Osteoarthritis Index (WOMAC) will be collected before clinical trial, 3 weeks after procedure, 6 weeks after procedure, and 4 weeks after the end of procedure. Outcome measurements and the following treatment schedules are summarized in Table 1.

#### Primary outcome measure

2.5.1

##### Visual analogue scale score (VAS)

2.5.1.1

VAS is a 10 cm measurement instrument to determine the severity of pain.^[16]^ A number ranging from 0 to 10 on both ends of the straight line is written down in words from no pain (0) to severe pain (10). The participant will mark on a straight line according to the degree of pain, and the investigator will measure the length to evaluate the pain.

#### Secondary outcome measures

2.5.2

##### Short form McGill pain questionnaire (SF-MPQ)

2.5.2.1

SF-MPQ is an instrument that summarizes the popular McGill pain questionnaire with mixed VAS, descriptive scale, and present pain intensity (PPI). The descriptive scale is based on 15 selected words, including 11 items in the sensory domain and 4 items in the emotional domain. The score is set from 0 to 3 (0-no symptoms, 1-mild, 2-moderate, 3-severe). The total score is obtained by summing the individual scores of all 15 items, with higher scores indicating more severe knee pain. PPI measures current pain severity in 6 levels (0-no pain, 1-mild, 2-discomforting, 3-depressing, 4-horrible, 5-excruciating).^[17]^

##### Western Ontario and McMaster universities osteoarthritis index (WOMAC)

2.5.2.2

The WOMAC score is a standardly used questionnaires to evaluate the pain and condition of patients with osteoarthritis of the knee and hip, including stiffness, pain, and physical functioning of the joints. It consists of 24 questions divided into 3 subscales. The index measures 2 questions for stiffness (score range 0–8), 5 questions for pain (score range 0–20), and 17 questions for physical function (score range 0–68). The total score is 96; higher scores indicate worse stiffness, pain, and functional limitations.^[18]^

### Adverse events and safety

2.6

Adverse events are defined as undesirable and unintended signs, symptoms, and diseases that develop after treatments in this clinical study process and are not necessarily caused by this clinical study. If a serious adverse event (SAE) occurs during the study, the treatment of the participant is temporarily suspended in the clinical trial, and if continuous treatment is deemed to be dangerous to the participant and if the adverse event is related to the intervention, the participant's participation in the clinical trial is discontinued. We will confirm the safety of TEA treatment by measuring blood tests and biochemical tests at the screening and after the termination of acupuncture (visit 7, visit 13) for patients. We will check the red blood cell (RBC) count, total white blood cell (WBC), hemoglobin, hematocrit, differential count, erythrocyte sedimentation rate (ESR), platelet, aspartate aminotransferase (AST), alanine aminotransferase (ALT), blood urea nitrogen (BUN), creatinine level, C-reactive protein (CRP), prothrombin time (PT), partial thromboplastin time (PTT), serum sodium level, serum potassium level, and serum chloride level.

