#### Exclusion criteria

2.3.2

(1)Those who had surgery on the knee due to osteoarthritis or other injuries(2)Those who received intraarticular injection of phototherapy, steroids, or hyaluronic acid within the last 3 months(3)Those with serious psychiatric problems(4)Those in need of adrenocortical hormones or other nonsteroidal anti-inflammatory analgesic drug treatment due to other medical conditions(5)Those with skin allergies, skin ulcers, or skin infections(6)Insulin injecting diabetic patients(7)Those using anticoagulants(8)Those elevated liver function tests (ALT, AST), more than 3 times the normal value(9)Those with abnormal findings on renal function test(10)Those who are deemed inappropriate for the study by the person in charge

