### Withdrawal and dropout

2.7

All participants will have the right to withdraw from the study at any time. Participation will be ended at any phase if the subject refuses to continue, withdraws consent, or violates the inclusion or exclusion criteria. In addition, the investigator records the completion of the study by the entire participant in the clinical trial and records the reasons for the discontinuation of the procedure.

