#### Statistical analysis

2.10.2

This statistical analysis is based on “Clinical Trial Statistics Guide (KFDA, 2000)” and the statistical package used is IBM SPSS Win ver. 19.0. The last observation carried forward method is used for missing data from drop-outs. For statistical significance, the significance level is set at 5%, and ITT (intention-to-treat: intent-to-treat analysis) analysis and PP (per protocol) analysis are conducted for all data analyses. ITT analysis is applied in principle.

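### After a serious adverse event, section 2.6 ends participation only if continuing is dangerous and the event is related; danger alone should stop study treatment, and follow-up should continue

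*Protocol article*

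**What the plan says.** Section 2.6 (Adverse events and safety) defines adverse events broadly, noting that they "are not necessarily caused by this clinical study". It then sets two steps for an SAE.

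- First, whatever the cause, "the treatment of the participant is temporarily suspended in the clinical trial".
- Second, a further step is tied to a double condition: "if continuous treatment is deemed to be dangerous to the participant and if the adverse event is related to the intervention". Where this is met, the stated consequence is that "participation in the clinical trial is discontinued".

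Section 2.7 (Withdrawal and dropout) gives further grounds: "Participation will be ended at any phase if the subject refuses to continue, withdraws consent, or violates the inclusion or exclusion criteria". The exclusion criteria in 2.3.2 end with a general judgement, item (10): "Those who are deemed inappropriate for the study by the person in charge".

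Section 2.5 schedules outcomes "before clinical trial, 3 weeks after procedure, 6 weeks after procedure, and 4 weeks after the end of procedure". Section 2.10.2 states: "The last observation carried forward method is used for missing data from drop-outs". The same section makes ITT the leading analysis, with a per-protocol analysis alongside it.

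**The concern.** Whether it is dangerous to go on treating someone does not depend on what caused the event. A new illness that has nothing to do with the trial can still make repeated thread insertion or needling unsafe. Relatedness matters for reporting and for the safety comparison. It should not be a second hurdle before a permanent stop, and in this open-label trial it would be judged with the treatment known.

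The second issue is the action itself. The only permanent step named is leaving the trial. Stopping study treatment while continuing to measure outcomes is not offered. That turns a treatment decision into missing data, in an analysis that is meant to follow everyone as randomised.

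**Working it through.** There is no plan figure to reproduce on this point. The check is a reading of the rule, followed by a short count.

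**1. The rule in 2.6, case by case.** Let A be that continuing is deemed dangerous and B that the event is related. An SAE has occurred.

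| A (dangerous) | B (related) | What 2.6 requires |
|---|---|---|
| yes | yes | suspension, then end of participation |
| yes | no | suspension only |
| no | yes | suspension only |
| no | no | suspension only |

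The second row can occur, because the definition of adverse events in 2.6 includes events the study did not cause.

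**2. Does another section cover the second row?** In part.

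- Section 2.7 ends participation when an exclusion criterion is violated, at any stage and with no relatedness condition.
- Several criteria in 2.3.2 describe states that an unrelated SAE could bring about: need for steroids or NSAIDs for another condition (4), skin allergy, ulcer or infection (5), anticoagulant use (7), liver enzymes more than 3 times normal (8) and abnormal renal function (9).
- Item (10) can take in the rest, but only through a general judgement of suitability that mentions neither SAEs nor danger.

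What remains is a dangerous, unrelated SAE that meets none of (4), (5) or (7) to (9) and for which nobody invokes (10).

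**3. What is lost when participation ends.** Inputs: 20 participants per arm (2.10.1) and 4 scheduled assessments, of which 1 is baseline (2.5).

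- Share of an arm per participant removed: 1 / 20 = 5%.
- Post-baseline assessments: 4 − 1 = 3.
- Removed before the 3-week assessment: 3 lost. LOCF carries the baseline value forward, which scores the participant as unchanged throughout.
- Removed between the 3-week and 6-week assessments: 3 − 1 = 2 lost.
- Removed after the 6-week assessment but before the last one: 3 − 2 = 1 lost.

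This count assumes that ended participation means no further outcome assessments, which is its ordinary meaning; the article does not say otherwise.

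**4. Which case the loss belongs to.** In 2.6 the loss arises in the first row (dangerous and related), where the rule fires. In the second row 2.6 removes nobody, so it causes no LOCF loss there; any loss in that row comes from an exit under 2.7.

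**The case against.** The strongest reply is that the wording leaves no participant on dangerous treatment. Every SAE suspends treatment, and no sentence says that treatment resumes. Section 2.7 is mandatory and reaches many of the clinical states in question without asking about cause. The repeated conditional may also be loose English for two separate triggers. And a journal article can leave detailed SAE handling to the full protocol.

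Much of this stands. A reader might infer that the protocol sends a participant back to dangerous treatment, or offers no way out, whenever the SAE is called unrelated. The documents support neither inference: the suspension has no stated end, and 2.7 with the exclusion criteria gives a route. A reader might also attach the LOCF loss to the unrelated case, but under 2.6 it belongs to the case where the rule fires.

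The reply does not remove the point. This is a stated condition, not a detail left out, and its plain reading requires both parts. If two triggers were meant, the sentence still needs correcting. The route through 2.7 depends on which criterion happens to be met, or on a general judgement, and it too ends participation as a whole.

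**Conclusion.** The point holds as a minor correction. On the plain reading of 2.6, a judgement of danger alone leads to no permanent stop under that section when the SAE is called unrelated. The residual gap is small, for the reasons given above.

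The separate weakness also holds: when the rule fires, it takes the participant out of the trial, at a cost of 5% of an arm and up to 3 post-baseline values each, replaced by LOCF in the ITT analysis. How often this would happen cannot be said. The article gives no SAE rate, and the chance of any SAE at all would not measure the dangerous-but-unrelated subset. Sample size, alpha and power are unaffected.

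The conclusion rests on two readings: that the two conditions are joint, and that ended participation ends outcome collection.

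**What to change.** Reword the SAE sentence in 2.6 along these lines: *If an SAE occurs, study treatment is suspended. If continuing is deemed dangerous to the participant, study treatment is permanently stopped, whatever the cause of the event. Relatedness is assessed and recorded separately. The participant remains in the scheduled outcome and safety assessments unless consent is withdrawn.* If the authors intended relatedness to be a trigger in its own right, it can stay as an additional ground for stopping treatment.

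Align 2.7 at the same time, so that an exclusion criterion newly met after randomisation stops study treatment and not follow-up. Without this, someone started on anticoagulants after an SAE would be kept in follow-up by 2.6 and removed by 2.7.

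The cost is a minor amendment to two short sections, with no extra participants and no assessments beyond those already scheduled. The downside is that the ITT data will contain some assessments made off treatment, which should be recorded as such.

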### Withdrawal and dropout

2.7

All participants will have the right to withdraw from the study at any time. Participation will be ended at any phase if the subject refuses to continue, withdraws consent, or violates the inclusion or exclusion criteria. In addition, the investigator records the completion of the study by the entire participant in the clinical trial and records the reasons for the discontinuation of the procedure.

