#### Sample size

2.10.1

This clinical trial is a pilot study, and will prepare for the primary confirmation stage and basic data about prudence in the study and clinical results before the large sample size study. Hence, rather than following the separate sample counting criteria, 20 participants were selected (20% dropout rate considered) for the experimental and control groups.

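### Section 2.7 ends participation for an eligibility breach at any stage, so randomised patients can lose follow-up that the lead ITT analysis needs

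*Protocol article*

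**What the plan says.** Section 2.7 (Withdrawal and dropout) gives the rule: "Participation will be ended at any phase if the subject refuses to continue, withdraws consent, or violates the inclusion or exclusion criteria". After that it provides only for documenting who completed the study, and the investigator "records the reasons for the discontinuation of the procedure".

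Section 2.3.3 (Randomization) applies the selection criteria before assignment. Section 2.3.2 lists exclusions that can also arise later, among them "Those who received intraarticular injection of phototherapy, steroids, or hyaluronic acid within the last 3 months". Knee surgery, skin infection, raised liver enzymes and abnormal renal function are also on that list.

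Section 2.10.2 (Statistical analysis) says that "ITT (intention-to-treat: intent-to-treat analysis) analysis and PP (per protocol) analysis are conducted for all data analyses" and that "ITT analysis is applied in principle". For incomplete data it says: "The last observation carried forward method is used for missing data from drop-outs". Outcomes are due at baseline, week 3, week 6 and 4 weeks after treatment ends, which is week 10 (section 2.5). The trial is open label (section 2.9).

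**The concern.** Eligibility criteria decide who may be randomised. A rule that applies them at every later stage can remove people because of what happens to them after allocation. Some of those events may be related to pain or to the procedure. A participant who is doing badly may receive a joint injection, and a skin infection may follow needling. The two arms receive different procedures and the allocation is known, so breaches may occur, or be judged to occur, more often in one arm.

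If participation ends, the remaining VAS, SF-MPQ and WOMAC values are missing, and an older value stands in for them. That loss is avoidable, because the participant may be quite willing to complete the questionnaires. It also matters for the pilot's own purpose. Dropout would look higher than it needs to be, and the VAS changes passed on to the larger trial would rest partly on carried values.

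**Working it through.** **1. Does the rule reach randomised participants?** Section 2.3.3 checks the criteria before assignment. Section 2.7 places no time limit on a breach. It therefore covers both an entry error found late and a criterion newly met after allocation.

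**2. Does it end more than treatment?** Section 2.6 uses two separate terms for serious adverse events. Treatment is suspended first, and participation is discontinued only if further conditions are met. Section 2.7 uses the stronger term, participation, with no further condition.

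**3. Can a breach arise during the study?** The study runs 6 + 4 = 10 weeks, which is shorter than the 3-month look-back for injections. A listed joint injection at any time after randomisation therefore still lies within that look-back at every remaining assessment. Knee surgery during the study also meets an exclusion item. Section 2.6 repeats AST, ALT, BUN and creatinine after treatment. Read literally, an abnormal result at that point could meet the liver or renal item and end participation before week 10, although section 2.6 sets its own conditions for discontinuation after a serious adverse event.

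**4. What replaces the lost values?** Under LOCF, removal before week 3 carries baseline to weeks 3, 6 and 10. Removal between weeks 3 and 6 carries the week-3 value. Removal after week 6 carries the week-6 value to week 10.

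**5. How large could the effect be?** The plan gives 20 per arm: "20 participants were selected (20% dropout rate considered) for the experimental and control groups". It gives no effect size, SD or expected number of breaches, so there is no figure of its own to reproduce. The gap g between carried and true VAS is assumed to be 1 to 2 cm.

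Shift in one arm's mean = (number removed / 20) × g:

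| Removed | Share | Shift at g = 1 cm | Shift at g = 2 cm |
|---|---|---|---|
| 1 | 5% | 0.05 cm | 0.10 cm |
| 2 | 10% | 0.10 cm | 0.20 cm |
| 4 | 20% | 0.20 cm | 0.40 cm |

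Between-group bias, with the same g in both arms = (share in one arm − share in the other) × g:

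- 10% and 10%: 0
- 20% and 10%: 0.10 × 1 to 0.10 × 2 = 0.1 to 0.2 cm
- 20% and 0%: 0.20 × 1 to 0.20 × 2 = 0.2 to 0.4 cm

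Equal removal is not enough by itself. With 10% removed in each arm but gaps of 2 cm and 1 cm, the bias is 0.10 × 2 − 0.10 × 1 = 0.10 cm. The sign of g is not known either. It is near zero for someone who has not changed, and it takes opposite signs for someone who later improves and someone who later worsens.

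**6. Test of the wording.** VAS 4 to 7 is an inclusion criterion (section 2.3.1). For a normal follow-up VAS with assumed mean 3.0 to 5.5 and SD 1.5 to 2.0, the share outside 4 to 7 runs from 0.16 + 0.16 = 32% (mean 5.5, SD 1.5) to about 75% (mean 3.0, SD 1.5, nearly all below 4). Nobody would apply the rule this way. The check shows only that the sentence lacks a limit to baseline.

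**The case against.** The strongest objection is that the natural reading of section 2.7 is an entry error discovered late, and that a condensed article need not describe follow-up after discontinuation. The first part is reasonable but is not what the sentence says. The second would succeed if the point rested on silence. It rests instead on a stated rule that ends participation, and a site following it as written would have no basis for further assessments. It remains true that the document does not expressly forbid them.

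Three stronger readings are tempting, and the documents do not support them.

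- **That the rule contradicts ITT.** Ending participation is not exclusion from the analysis. Section 2.10.2 keeps ITT as the lead analysis and imputes for drop-outs, so all randomised participants can remain in their allocated arms. What is lost is outcome data.
- **That treatment failures are systematically sent to LOCF.** Section 2.7 does not mention failure. The steroid and NSAID exclusion is confined to need arising from other medical conditions, so taking an analgesic for a painful study knee is not clearly a breach. Injection and surgery are plausible routes, but no frequency is given. On the literal VAS reading responders would be removed too, so the direction is not fixed.
- **That declining further sessions ends all follow-up.** Refusing to continue may simply mean refusing the study. The text does not settle this.

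It is also fair to say that a sizeable shift needs a gap of 1 to 2 cm and unequal removals or unequal gaps. A participant who has not improved contributes little, because the carried baseline is then close to the truth.

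**Conclusion.** The point holds as a weakness in a stated rule. Followed as written, section 2.7 creates avoidable missing outcomes among randomised participants and passes them to LOCF, in an open-label trial whose lead analysis is ITT and where "the significance level is set at 5"%. It undermines that analysis without contradicting it.

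No figure in the plan is shown to be wrong. On an assumed gap of 1 to 2 cm, each removal moves an arm mean by 0.05 to 0.10 cm. The between-group effect is zero if removals and gaps match across arms. The true size and direction cannot be obtained from the document. The change is still worth making, because it is cheap and the lost data cannot be recovered afterwards.

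**What to change.** Amend section 2.7 as follows.

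- State that a breach of an eligibility criterion, whether found or arising after randomisation, does not end outcome follow-up.
- Collect VAS, SF-MPQ and WOMAC at whichever of weeks 3, 6 and 10 remain, unless the participant withdraws consent to follow-up. Record separately whether treatment stopped, whether follow-up stopped, and why.
- Analyse the participant in the allocated arm under ITT, and handle the breach only in the per-protocol set already planned in section 2.10.2.
- Reconcile sections 2.6 and 2.7 on when treatment and participation end. Whether study treatment stops is for the investigators, and this point takes no position on it.

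The cost is a short amendment and a few questionnaires at visits already scheduled. The downside is that some outcome data will follow off-protocol treatment. The ITT comparison will then include the effect of that treatment, and the report should say so.
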